# NutriBrain: protocol for a randomised, double-blind, controlled trial to evaluate the effects of a nutritional product on brain integrity in preterm infants

**DOI:** 10.1186/s12887-021-02570-x

**Published:** 2021-03-17

**Keywords:** Probiotics, Prebiotics, Glutamine, Preterm infants, Brain development, Randomised controlled trial

## Abstract

**Background:**

The gut microbiota and the brain are connected through different mechanisms. Bacterial colonisation of the gut plays a substantial role in normal brain development, providing opportunities for nutritional neuroprotective interventions that target the gut microbiome. Preterm infants are at risk for brain injury, especially white matter injury, mediated by inflammation and infection. Probiotics, prebiotics and L-glutamine are nutritional components that have individually already demonstrated beneficial effects in preterm infants, mostly by reducing infections or modulating the inflammatory response. The NutriBrain study aims to evaluate the benefits of a combination of probiotics, prebiotics and L-glutamine on white matter microstructure integrity (i.e., development of white matter tracts) at term equivalent age in very and extremely preterm born infants.

**Methods:**

This study is a double-blind, randomised, controlled, parallel-group, single-center study. Eighty-eight infants born between 24 + 0 and < 30 + 0 weeks gestational age and less than 72 h old will be randomised after parental informed consent to receive either active study product or placebo. Active study product consists of a combination of *Bifidobacterium breve *M-16V, short-chain galacto-oligosaccharides, long-chain fructo-oligosaccharides and L-glutamine and will be given enterally in addition to regular infant feeding from 48 to 72 h after birth until 36 weeks postmenstrual age. The primary study outcome of white matter microstructure integrity will be measured as fractional anisotropy, assessed using magnetic resonance diffusion tensor imaging at term equivalent age and analysed using Tract-Based Spatial Statistics. Secondary outcomes are white matter injury, brain tissue volumes and cortical morphology, serious neonatal infections, serum inflammatory markers and neurodevelopmental outcome.

**Discussion:**

This study will be the first to evaluate the effect of a combination of probiotics, prebiotics and L-glutamine on brain development in preterm infants. It may give new insights in the development and function of the gut microbiota and immune system in relation to brain development and provide a new, safe treatment possibility to improve brain development in the care for preterm infants.

**Trial registration:**

ISRCTN, ISRCTN96620855. Date assigned: 10/10/2017.

**Supplementary Information:**

The online version contains supplementary material available at 10.1186/s12887-021-02570-x.

## Background

In recent years a growing body of evidence has developed supporting the existence of a microbiome-gut-brain-axis [1–3]. The gut microbiota connect to the brain through different mechanisms that are not yet fully elucidated but likely consist of neural, immunological and endocrine pathways [4, 5]. Research has shown that bacterial colonisation of the gut is important for normal brain function making the gut microbiome a possible target for nutritional neuroprotective interventions. Studies in germ-free animals and animals exposed to bacterial infections suggest that the gut microbiota play a role in anxiety and behaviour [6, 7]. Interestingly, studies in mice have demonstrated beneficial effects of probiotics on brain function, mood and behaviour [6, 8], whilst studies in germ-free mice have established that altered behavioural responses could be normalised if normal gut microbiota was reconstituted early in life. Normalisation in adulthood failed to exert such an effect [9, 10]. These findings suggest a ‘window of opportunity’ early in life for the gut microbiota to influence brain development and behaviour that could be used in the care for preterm infants. Preterm infants are at risk for brain injury, especially white matter injury, because of their extra-uterine life during a period of significant brain development [11]. White matter injury, and also other brain injury, can cause disrupted development of the white matter and subsequent deteriorated white matter integrity. The impact of nutrition on brain growth and cognition in preterm infants is increasingly acknowledged, [12–17] although randomised controlled trials of many single nutritional components have demonstrated no clear positive effect of individual components on brain development of preterm infants so far [18]. For the current study, the active intervention will consist of three nutritional components combined: probiotics, prebiotics and glutamine. These three components have already demonstrated positive effects in preterm infants individually.

### Probiotics

Probiotics are living micro-organisms that in adequate amounts provide health benefits for the host, [19] using different mechanisms including alteration of the gut microbiota, increase in the gut epithelial barrier function and modulation of the immune system [20]. A number of clinical trials showed significant reduction in the incidence of severe necrotising enterocolitis (NEC), all-cause mortality and sepsis in preterm infants who received probiotics compared to controls [21–23]. Reduction of the risk of NEC and all-cause mortality, but not sepsis, in infants supplemented with probiotics compared to placebo was confirmed in a Cochrane review evaluating 24 studies and over 5000 infants [24]. A second systematic review and meta-analysis including 25 studies and over 6000 infants did find a reduction of the risk of sepsis in preterm infants who received probiotics compared to placebo, although many included studies were of low methodological quality [25]. For our study the probiotic strain *Bifidobacterium breve* (*B. breve*) M-16V was selected. A large body of evidence from both animal studies and clinical trials in infants shows that administration of *B. breve* M-16V is associated with beneficial health effects including modulation of the gut microbiota, [26, 27] reduced levels of pathogenic bacteria, [27] reduced inflammatory reactions, [28, 29] and prevention of infection and NEC, [29, 30] summarised in a recent review [31].

### Prebiotics

Prebiotics are non-digestible food components that can modify gut microbiota by being selectively fermented by beneficial intestinal bacteria, such as *Bifidobacteria* [32, 33]. The combination of probiotics and prebiotics can therefore work synergistically [34]. For this study short-chain (sc) galacto-oligosaccharides (GOS) and long-chain (lc) fructo-oligosaccharides (FOS), two of the most widely studied prebiotics, will be used. Oligosaccharides represent an important component of human milk and, interestingly, especially of preterm human milk [35]. They have multiple beneficial qualities including an ability to alter the gut microbiota and immunomodulatory functions [32]. Because of their presumed health benefits prebiotic oligosaccharides are supplemented to preterm formula as part of routine care. Several studies evaluated the effect of adding oligosaccharides to preterm infant formula on growth, intestinal microbiota, gastrointestinal transport time, stool frequency and stool consistency [36–39]. Prebiotic supplementation resulted in increased *Bifidobacteria* counts [36] and fewer intestinal pathogens, [37] accelerated gastrointestinal transport, [38, 39] increased stool frequency, [36] and reduced stool viscosity [38] in infants compared to controls. Furthermore, a meta-analysis showed a positive effect of prebiotic supplementation in preterm infants on the incidence of sepsis, mortality, length of hospital stay and time to reach full enteral feeding, but not on the incidence of NEC [40]. Supplementation with prebiotics may also modify the systemic inflammatory response by improving the balance between pro- and anti-inflammatory cytokines, with one study reporting lower cytokine levels in infants fed prebiotic oligosaccharides as a supplement to human milk or preterm formula compared to the control group, shortly after the start of the intervention [41].

### L-glutamine

L-glutamine is considered an important fuel for rapidly dividing cells such as enterocytes and lymphocytes and plays a substantial role in maintaining functional integrity of the gut [42, 43]. Previous studies in preterm infants have shown a positive effect of supplementation with L-glutamine on gastrointestinal dysfunction, [44] severe neurologic sequelae, [44] serious neonatal infections, [45, 46] head circumference [47] and brain volumes [48]. The effect of parenteral and enteral supplementation with glutamine on mortality and morbidity in preterm infants was evaluated in a Cochrane review. Although no overall difference in mortality or morbidity was found, a subgroup meta-analysis including studies with enteral supplementation only (6 studies, 1095 infants) showed a lower incidence of invasive infection in the glutamine supplemented group compared to controls (RR 0.76, 95% CI 0.64–0.89, I^2^ = 56%) [49]. Although this result is based on subgroup analysis and should therefore be interpreted with caution, it emphasises the possible effect of L-glutamine on preventing inflammation and its subsequent potential as a neuroprotective agent. 

To date there is no literature on the combined effects of *B. breve* M-16V, scGOS/lcFOS and L-glutamine in preterm infants nor their impact on neonatal brain development. However a recent preclinical trial with preterm born piglets (*n* = 40) showed those supplemented with *B. breve* M-16V, scGOS/lcFOS and L-glutamine demonstrated increased cognitive performance as assessed in the T-maze compared to control piglets [50]. Additionally, on ex vivo diffusion imaging piglets in the intervention group showed increased maturation of the white matter fibre bundles and advanced grey matter microstructural maturational processes compared to control piglets [50]. We hypothesize that this combination of probiotics, prebiotics and L-glutamine may act synergistically and will therefore combine these components in this study. We hypothesize that scGOS/lcFOS will promote survival of *B. breve* M-16V and improve its effect on immunomodulation and intestinal integrity in addition to its expected intrinsic benefits. L-glutamine may further enhance these favourable effects. This combination may decrease serious neonatal infections and subsequently reduce white matter injury. This study aims to evaluate the benefits of *B. breve* M-16V, scGOS/lcFOS and L-glutamine on white matter microstructure integrity (i.e., development of white matter tracts) at term equivalent age in very and extremely preterm born infants.

## Methods

### Study design and study setting

The NutriBrain study is a double-blind, randomised, controlled, parallel-group, single-center study. The aim of this study is to investigate the effect of the test product versus control given to preterm infants born at 24 + 0 to < 30 + 0 weeks gestational age (GA) on white matter microstructure integrity measured as fractional anisotropy (FA) assessed using magnetic resonance diffusion tensor imaging (DTI) at term equivalent age (TEA) and analysed using Tract-Based Spatial Statistics (TBSS).

This study will be conducted at the University Medical Center (UMC) Utrecht and seven regional hospitals in The Netherlands (details can be found in the ISRCTN registry). Due to the GA of included infants (extremely and very preterm infants) the inclusion, randomisation and study start will take place at the level III neonatal intensive care unit of the UMC Utrecht, a large tertiary care hospital in The Netherlands. If the condition of the infant has improved to the extent that intensive care is no longer necessary, they can be transferred to a level II or level I neonatal unit at a participating regional hospital and will continue to be followed up (under supervision of the principal investigator). Each hospital to which an infant is transferred will be asked to provide information relating to the study parameters during the infant’s stay.

### Study population

Infants with a GA of 24 + 0 to < 30 + 0 weeks that are less than 72 h old are eligible for inclusion. A complete overview of inclusion and exclusion criteria is shown in Table 1.

**Table 1 Tab1:** Overview of inclusion and exclusion criteria

**Inclusion criteria**	
1) Gestational age of 24 + 0 to < 30 + 0 weeks	
2) Less than 72 h old and the intention to receive the first administration of study product between 48 and 72 h after birth	
3) Written informed consent from custodial parent(s)	
**Exclusion criteria**	
1) Any relevant proven or suspected chromosomal anomaly, metabolic disorder, genetic syndrome or congenital central nervous system malformation	
2) Presence of any gastrointestinal malformation	
3) No realistic prospect of survival (e.g. severe brain injury), at the discretion of the attending physician	
4) Concomitant participation in other intervention studies (for example, but not exclusively, those studies involving investigational or marketed nutritional or pharmaceutical products) that could impact on the main outcome parameters and/or infant safety	
5) Expected or foreseen inability of the infant and/or their families to adhere to protocol instructions	
6) Admission from an extra regional hospital, unless that hospital is a study site	
7) Current use of gastric acid inhibitors: H_2_-receptor antagonists (including ranitidine) or proton pump inhibitors (including omeprazole)	

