### Treatment allocation and blinding

After eligibility has been assessed and informed consent has been obtained the infant will be enrolled in the study. To randomise an infant to the study, investigators will log in to the electronic Case Report Form (eCRF) and follow the prompts to input infant data. Only investigators specifically trained to perform randomisation will have access to the eCRF. Based on the order in which infants enter the study and stratified by sex, the infant will be assigned a randomisation number by the eCRF system. The infant will receive the product with the code corresponding to his/her randomisation number. Twins and multiple births will be allocated to the same study group. Investigators, all site staff including medical and nursing staff and supporting staff who prepare the infant feedings, and parents will be unaware of treatment allocation.

The randomisation sequence will be generated using the PLAN procedure of SAS statistical software (Enterprise Guide version 4.3 or higher) by a statistician from Danone Nutricia Research who has no further involvement in the conduct of the trial. The permuted block randomisation will be stratified by sex (boys, girls) with a 1:1 allocation ratio of test and control product. The block size or sizes and whether the block size(s) will be fixed or randomly varied will be decided by and known only to the statistician. The packaging of the test and control products will be identical in appearance. The study product for each infant will be labelled using a unique random number according to the randomisation schedule. These random numbers will have been linked (via a code) beforehand to either test or control product. Which numbers correspond to which treatment will only be known to the supplies manager at Danone Nutricia Research.

The randomisation code will be broken after analysis of the primary outcome and other outcomes collected until TEA. Assessors, parents, hospital staff and all those involved in the conduct and/or decision making of the follow-up phase will remain blinded to study product allocation until follow-up database lock after the last infant has completed the study (24 months corrected age). In the case of a medical emergency that requires preliminary unblinding of study product, unblinding in the eCRF or with sealed unblinding envelopes stored at the UMC Utrecht will be possible.

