### Supplementation

Study product supplementation will start between 48 and 72 h after birth or, if the infant is clinically unstable as soon as possible thereafter, and will continue until 36 weeks postmenstrual age. If the infant is discharged home or fully breastfed before 36 weeks postmenstrual age supplementation will be stopped. Study product Part A will be administered enterally once per day as a single daily dose not supplemented to feeding or medication. The dosage of *B. breve* will depend on birth weight: Infants with a birth weight ≥ 1000 g will receive 3 × 10^9^ colony-forming units (cfu) per day; Infants with a birth weight < 1000 g will receive 1.5 × 10^9^ cfu per day, to be increased to 3 × 10^9^ cfu per day when they have reached enteral feeding intakes of 50 ml/kg/day. Study product Part B will be administered enterally supplemented to the regular milk feed (breast milk or preterm formula, depending on parents’ choice). Dosage will be increased in a stepwise fashion. Based on the infant’s weight, daily intake of enteral feeding and the desired (maximum) osmolarity of the feeding, a supplementation schema was created, starting with a minimum dosage of 0.05 g/day L-glutamine and 0.1 g/day scGOS/lcFOS and aiming for a final dose of 0.3 g/kg/day L-glutamine and 0.6 g/kg/day scGOS/lcFOS when the infant receives full enteral feeding (120 ml/kg/day for 1 day). The final dosages of L-glutamine and scGOS/lcFOS were based on the GEEF study [45] and CARROT study [51], respectively, in which supplementation was well tolerated.

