#### Secondary outcomes

White matter injury, measured with the white matter injury score according to Kidokoro et al., [57] which evaluates cystic lesions, focal signal abnormality, myelination delay, thinning of the corpus callosum, dilated lateral ventricles and volume reduction on T2- and T1-weighted MR images acquired at TEA.Brain tissue volumes (cerebellum, cortical grey matter, unmyelinated white matter, deep nuclear grey matter, ventricular volumes and extracerebral cerebrospinal fluid) and cortical morphology (sulcation index, cortical surface area and cortical thickness) assessed using the segmentation method of Moeskops et al. [58] of T2- and T1-weighted MR images made at TEA.The occurrence of serious neonatal infections (defined as culture proven or clinical sepsis with associated clinical symptoms; clinically significant NEC [i.e., Bell’s stage two or higher]; meningitis with or without positive culture; or pneumonia [positive culture of tracheal aspirate, bronchial secretion, or sputum positive for microorganisms with associated clinical symptoms]) [45, 51] until TEA.Serum concentrations of specific circulating inflammatory markers such as IL-6, IL-10, TNF-α and IL-8/CXCL8 measured with flow cytometry and Luminex at 7, 21 and 42 days postnatal, 30 and 36 weeks postmenstrual age, discharge to other hospital and TEA (optional, in a subgroup).Motor and cognitive development assessed with the Bayley Scales of Infant and Toddler Development, Third Edition, [59] at 24 months corrected age.

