### Data collection

All study data will be collected in a validated eCRF (VIEDOC, from Pharma Consulting Group during the intervention period; Castor during the follow up period). To guarantee data quality only trained study staff can enter data in the eCRF. Data will be collected and stored in line with data privacy laws, and details on data management are documented in the data management plan. Collected data will include: gender, GA, (birth) weight, (birth) length, (birth) head circumference, parental level of education, parental head circumference, score for Neonatal Acute Physiology – Perinatal Extension (SNAPPE-II), obstetric and perinatal details (such as presence of chorioamnionitis, prenatal medication, relevant maternal illnesses, Apgar scores and cord blood parameters), neonatal morbidity (such as infant respiratory distress syndrome, need for respiratory support, neonatal infections, patent ductus arteriosus, intraventricular haemorrhage and post haemorrhagic ventricular dilatation), neonatal medication, enteral and parenteral feeding characteristics and cumulative intake. Additionally stool samples will be collected at fixed time points to evaluate bacterial colonisation and the development of the microbiome and to be able to detect possible cross contamination with *B. breve* M-16V in infants allocated to the control group, using *B. breve* M-16V specific primers.

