### Statistical analysis

#### Primary outcome parameter and other MRI-derived parameters

TBSS analysis will be performed as previously described [61]. In summary, group comparisons will be performed with FMRIB Software Library’s Randomise tool using a general linear univariate model, [62] with family-wise error correction for multiple testing using threshold-free cluster enhancement with a significance level of *p* < 0.05 [63]. Group comparisons for volumetric analyses will be performed with ANOVA, with false discovery rate to correct for multiple testing. In all analyses GA at birth, postmenstrual age at time of MRI, birth weight Z-score and days of ventilation will be entered as covariates. These analyses have been used in several other observational and intervention studies conducted in the UMC Utrecht and other research groups, in preterm infants at TEA (mean and median GA of 28.7 weeks), [52, 64] healthy and asphyxiated full term infants, [65, 66] as well as children at school age (7.5–8.5 years and 12 years of age) [67–69].

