#### Safety and tolerance parameters, exploratory outcome parameters and secondary outcome parameters that are not derived from MRI assessment

Statistical analysis of continuous outcomes that are measured at more than one time point will be performed by means of linear mixed models analysis. Statistical analysis of discrete outcomes (dichotomous variables, ordered categorical variables and counts) will be performed using parametric (i.e., generalized linear models) or non-parametric methods. For other types of outcome parameters stratified tests (e.g., Cochran-Mantel-Haenszel test) and/or simple hypothesis testing methods (e.g., Chi-square or Fisher exact tests) will be employed. Details on the statistical analyses will be documented in a statistical analyses plan prior to database lock/unblinding.

Considering our relatively small sample size, it is possible that confounding factors for probiotic efficacy, such as antibiotic exposure, could be unevenly distributed between the active and placebo study group. Baseline characteristics will be evaluated at the start of the statistical analysis, and important confounding factors will be taken into account as covariates in the analysis. Analysis of the primary outcome parameter will be based on all included patients intended to treat with usable MRI according to DTI quality. Additionally, a per protocol analysis will be carried out for supporting purposes. Safety parameters will be analysed on the All Subjects Treated population. To account for possible cross contamination additional analyses will be performed to evaluate infants with and without *B. breve* M-16V colonisation. A *p*-value < 0.05 will be considered statistically significant.

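### The fixed covariates for the MRI analyses omit brain injury present before first study product, which costs avoidable precision at about 35 infants per arm

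*Protocol article*

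**What the plan says.** **Who enters.** In Table 1, acquired brain injury is reached only by exclusion 3: "No realistic prospect of survival (e.g. severe brain injury), at the discretion of the attending physician". Exclusion 1 concerns inborn conditions, among them "genetic syndrome or congenital central nervous system malformation". Survivable acquired injury is not excluded.

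**When product starts.** Supplementation section: "Study product supplementation will start between 48 and 72 h after birth or, if the infant is clinically unstable as soon as possible thereafter".

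**How arms are balanced.** Treatment allocation and blinding: "The permuted block randomisation will be stratified by sex (boys, girls) with a 1:1 allocation ratio of test and control product". Injury is not a stratification factor.

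**What the MRI models adjust for.** Statistical analysis, primary outcome and other MRI-derived parameters: "In all analyses GA at birth, postmenstrual age at time of MRI, birth weight Z-score and days of ventilation will be entered as covariates". A later paragraph adds: "Baseline characteristics will be evaluated at the start of the statistical analysis, and important confounding factors will be taken into account as covariates in the" (quote cut before its final word). That paragraph stands under a heading for outcomes not derived from MRI, but its next sentence concerns the primary outcome. Its example of a confounder is antibiotic exposure.

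**What is measured at term equivalent age.** Besides fractional anisotropy (FA), the white matter injury score includes "thinning of the corpus callosum, dilated lateral ventricles and volume reduction on T2- and T1-weighted MR images acquired at TEA". Ventricular volume is one of the volumetric outcomes.

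**What is recorded.** The Data collection section lists "patent ductus arteriosus, intraventricular haemorrhage and post haemorrhagic ventricular dilatation" among neonatal morbidity, with no timing relative to first product. Serial cranial ultrasound appears under Protocol compliance and missing data, where it helps define which infants have an MRI done only for the study.

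**The concern.** The product is expected to act through fewer serious infections and, through these, less white matter injury. Injury that is already there at 48–72 h cannot be prevented by that route, yet it can lower FA, raise the injury score and enlarge the ventricles at term equivalent age. The Background section states the link between brain injury and poorer white matter integrity, so this is a prognostic factor on the protocol's own premise, and it can be present before treatment begins.

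Left out of the model, its variation goes into the residual, and a chance difference between arms in the number of injured infants is not corrected. The sample size rests on 35 evaluable infants per arm, so a few infants can matter. The fixed list does include days of ventilation, which can accrue after randomisation, but no measure of injury before product.

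**Working it through.** **Plan's own figure.** Sample size section: 35 evaluable per group, 70 in total, 88 randomised. 70/0.80 = 87.5, which rounds up to 88. The loss rate is not stated; 88 implies 1 − 70/88 = 20.5%. The 35 per group comes from a cited simulation study, and the article gives no SD or power for it, so it cannot be re-derived here.

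**Inputs.** n = 35 per arm (protocol). Prevalence p of injury before first product and its effect d, in SDs within injury status, are **assumptions**: p = 10–30%, d = 0.5–1.5. A single mean-FA contrast between independent infants stands in for the voxelwise test.

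**Formulas**
- SD of the chance difference in injury prevalence: √(2p(1−p)/35)
- Typical shift in the group difference: d times that SD
- Outcome variance without adjustment: V = 1 + p(1−p)d²
- Share of variance explained by injury: (V − 1)/V
- Cut in standard error from adjustment: 1 − 1/√V

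| p | d | SD of imbalance | Shift (SD) | V | Share explained | Cut in SE |
|---|---|---|---|---|---|---|
| 10% | 0.5 | 7.2 points | 0.036 | 1.0225 | 2.2% | 1.1% |
| 20% | 1.0 | 9.6 points | 0.096 | 1.16 | 13.8% | 7.2% |
| 30% | 1.5 | 11.0 points | 0.164 | 1.4725 | 32.1% | 17.6% |

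**The shift is already inside the standard error.** Middle case: unadjusted SE = √(2 × 1.16/35) = 0.257; adjusted SE = √(2/35) = 0.239. And 0.239² + 0.096² = 0.057 + 0.009 = 0.066 = 0.257².

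**Chance imbalance.** By exact binomial calculation, the arms differ by at least 4 injured infants with probability 15.9% at p = 10% and 29.4% at p = 20%.

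**Power.** With injury adjusted for, 35 per arm gives 80% power at a difference of (1.96 + 0.84) × √(2/35) = 0.67 SD. Without adjustment, power for that difference is 79.1% (p = 10%, d = 0.5) and 73.9% (p = 20%, d = 1). Restoring 80% would take 35 × 1.0225 = 35.8, so 36, and 35 × 1.16 = 40.6, so 41 evaluable infants per arm.

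**Type I error.** In simulation without adjustment it was 5.1% (p = 10%, d = 1), 4.8% (p = 20%, d = 1.5) and 4.8% (p = 25%, d = 2). There is no inflation.

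**The case against.** The strongest reply is that nothing here is invalid. Randomisation balances early injury in expectation, and omitting a prognostic covariate leaves the test at its nominal level. A reader might infer from the eligibility rule that the MRI comparison is biased, or that false positives are more likely. The documents do not support that, and the simulation contradicts it.

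Second, it would be too strong to say that the plan cannot account for early injury. The confounder clause plausibly reaches the primary outcome, sets no formal imbalance threshold, and is followed up in a statistical analysis plan to be written before database lock or unblinding. The code stays unbroken until the outcomes to term equivalent age have been analysed, which limits covariate choice informed by treatment. This stands in part. Even so, the clause does not name injury and leaves its use to an inspection of the data, whereas the MRI section fixes a list without it.

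Third, the gain is assumed, and it is an upper bound. The working treats injury as unrelated to the existing covariates and uses one effect range for FA, injury score and ventricular volume. Gestational age and days of ventilation may carry part of the same information. This stands.

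Fourth, the data may not be ready to use. The article does not show that ultrasound findings are dated relative to first product. This also stands, and it shapes the fix.

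**Conclusion.** The point holds as a matter of precision and prespecification. A factor that can be present before treatment, and that the protocol itself links to its primary outcome, is missing from the covariates fixed for all MRI analyses. The consequence is avoidable noise and uncorrected chance imbalance, with no systematic error in the comparison.

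Adjustment would cut the standard error by at most about 1% at the mild end of the assumed ranges, about 7% in the middle and about 18% at the far end. These figures rest on assumed prevalence and effect, on independence from the covariates already in the model, and on a single FA contrast. Overlap with gestational age or ventilation would make them smaller. The typical shift of 0.04–0.16 SD should not be read as an error on top of the standard error, because it is one of its components.

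The change is worth making because it is small and replaces a choice made after inspecting the data with a fixed one.

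**What to change.** In the section on the primary outcome and other MRI-derived parameters, add one prespecified binary covariate to the TBSS, volumetric and injury-score analyses: any haemorrhage or parenchymal injury on the last cranial ultrasound before first study product (yes/no).

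- Use only scans made before first product, so that later injury, which the product might affect, is not adjusted away.
- Confirm that ultrasound findings can be dated relative to first product.
- State before unblinding how infants without such a scan are handled, for example as a separate not-known level.

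**Cost.** One degree of freedom, or two with a not-known level, and retrieval of scan dates from routine records. A finer grading would cost more: three injury levels plus not-known use 3 degrees of freedom, and at 10% prevalence only about 7 of 70 infants would be spread over the injury levels. Eligibility does not change.
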